#### Counselor and Study Scheduler Recruitment, Training and Supervision

The telephone counselors are women with Master's level education or counseling experience. The Counselors train for two weeks in the detailed counseling protocol by a clinical psychologist and an experienced telephone counselor. Training includes: building adequate skills using the CATI system, counseling protocol and materials; role-playing all aspects of the intervention from staging patients to action planning and familiarizing the Counselor with the scheduling procedures. Study Schedulers are Bachelor's prepared Research Assistants with some research experience. The initial training for the Study Scheduler takes 20 hours. Both Counselors and Study Schedulers received didactic presentations on research methods, study goals, breast cancer and mammography screening, systems-based interventions to increase mammography use, screening rates in minority populations and role-playing with study staff and "mock" patients. Selected telephone calls are audio taped and reviewed by the study project manager for quality control and to insure fidelity to protocol. Appropriate refresher/corrective sessions are undertaken as needed.

#### Repeat interventions (booster doses)

There are very few studies examining the effect of repeat interventions [13,50-53]. Since the intervention period will span 48 months, we will be able to evaluate the booster effect more fully.

### Outcomes

The primary outcome is the proportion of women continuously enrolled for ≥24 months who have had ≥1 mammogram in the last 24 months. This measure mimics the standard HEDIS (Healthcare Effectiveness and Data Information Set) measure used by most health plans and systems to track mammography utilization, although the HEDIS measure is usually applied only to women age 50-69. The measure is a cross-sectional, prevalence measure that can be applied in a series of static "snapshots" to a dynamically changing population like the one in our study and in any typical health plan.

The secondary outcomes are 1) the number of women in each arm requiring repeat interventions and 2) the immediate outcomes (change in stage of readiness, mammography scheduling for those in the RC and ETTC arms during calls) and short term outcomes (receiving a mammogram within 3 months) following the interventions, for all women receiving the interventions for the first time, adjusted as needed by appropriate covariates (e.g. age, time to last mammogram, marital status and other factors).

The main cost-effectiveness outcome is the incremental cost-effectiveness of each intervention combination, that is, the difference in the percentage of eligible women with mammograms divided by the difference in total cost for each intervention pair. The study also measures separately the startup and operating costs of each intervention.

### Data Collection and Management

During the four-year intervention period the claims database and the electronic health record data base are searched weekly to determine eligibility of women to receive a reminder letter. Study staff enter data on study enrollment when they receive information from PCPs and/or from women relevant to enrollment. The only data required for primary outcome measures on women enrolled in the study are duration of enrollment in FCHP/FC, dates of mammograms, and birth date for developing age-specific outcomes.

Secondary analyses will include subgroup analyses involving the primary outcome, analyses involving secondary outcomes (e.g. change in stage of readiness from beginning to the end of reminder and ETTC calls, completion of scheduled mammograms and time from intervention to mammogram completion) and other analyses requiring independent variables collected from the FCHP database and during all calls from and to subjects. Medicare and Medicaid insurance coverage, history of claims for preventive checkups and other screening tests (e.g. Pap smears, cholesterol, colon cancer screening) will be obtained from FCHP claims databases and the electronic health record database to compare adherence to mammography recommendations to the utilization of other preventive services. (Table 5 shows all of the data sources)

**Table 5 T5:** Data Sources for Analysis

Data Sources	Primary Outcome Analysis	Secondary Data Analyses	Process Analysis
FCHP and FC Membership Database	X	X	X

FCHP Claims Database and Electronic Health Record database	X	X	X

Fallon Clinic Scheduling System		X	X

Patient Survey (Administered to subjects calling the Study Scheduler or receiving reminder or ETTC calls)		X	

ETTC and Reminder Call CATI System & Tracking Database		X	X

Phone Call Logs			X

PCP Approvals for Patient Enrollment	X	X	X

Patient Refusals of Enrollment	X	X	

The cost effectiveness analysis will measure all costs from the provider perspective. We will estimate start-up costs and fully staffed operational and cost estimates to give potential adopters a sense of the investment required to implement and maintain each intervention. Start up costs include database and software development and installation, equipment purchases, training costs, and overall administrative costs for the RC and ETTC interventions. Operational costs include staff and administration salaries, overhead costs (office space, phone, electric, etc.), office supplies, information system and equipment maintenance, and postage. We employ a "micro-costing" approach where units for each component of resource use are measured directly, a unit cost is applied for each and units are multiplied by unit cost to get cost estimates. Staff time and effort involved for all tasks in the intervention are measured using staff logs.

### Sample Size and Power

#### Power and Sample Size

Given, the typical size of the female population ages 51-84 at FCHP/FC of 25,000, we estimated there would be at minimum 15,000 women available for the analyses involving the primary outcome at each year. We explored power to detect differences in primary outcome among intervention groups under two scenarios. Based on findings from our EPICS study [27] we believe that it is reasonable to expect differences of 3-5% or greater across groups. Differences that are smaller would likely be of little interest to health plans. In the first scenario we assumed that the primary outcome in the RL group remains at 75%, as it is now and that the outcome in the RC group is 80% and in the ETTC 85%. In the second scenario we assumed these outcomes: RL 80%, RC 83% and ETTC 86%. With 15,000 in the sample (5,000 per group) there is greater than 99% power to detect the differences proposed or larger ones across groups under both scenarios. For the trends over time there will be approximately 90% power for an increasing trend over five years leading to a 5% increase in any group (e.g..75 to.80) based on Cochran-Armitage test of trend with power calculations described by Hintze [54]. Power calculations were carried out using Power Analysis and Sample Size (PASS) 2008.

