## Methods/design

### Study Design

#### Overall design

Figure 1 shows the overall design of the study. Beginning in July, 2009, all eligible women are automatically enrolled and randomized 1:1:1 to the three study arms. After approval by PCPs and passive consent, women are entered into the reminder study. The interventions (letters and calls) are directed only to women who have not had a mammogram in ≥ 18 months. The primary outcome is the proportion of all women who have been enrolled for ≥ 24 months with a mammogram within the previous 24 months. This outcome will be determined at five times, at baseline and at the end of each intervention year. Outcome at the end of the last intervention year will be the single most important result.

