### Statistical Methods

#### Primary Outcome Analysis: HEDIS-like measure over time

The unit of randomization and analysis is the individual woman. The primary outcome measure is the proportion of women continuously enrolled for 24 months with ≥1 mammogram in the past 24 months. This will be evaluated at the five measurement time points. The main study finding of interest will be the comparison of this proportion across groups after the last year of intervention (Year 4), because we believe this result best illustrates the magnitude of intervention effect that would be achieved in all future years. The second hypothesis is that the primary outcome measure may change differently over time in the telephone intervention groups because there may be some cumulative effect of repeated interventions on women who do not respond the first time. It is also possible that the interventions may become less effective when applied repeatedly to the same group of women over time. Changes in the composition of the patient population over time could also cause changes in the outcomes. We will estimate the trend over time of the primary outcome within each intervention group and compare the trends over time among the randomized groups. The third hypothesis is that lower age will be associated with a greater response to less intensive interventions. We will investigate this hypothesis through analyses assessing the interaction of subgroups and the intervention arms. To accomplish this and some related analyses involving the primary outcome, we will examine the interactions with intervention group of age, type of medical insurance, and time since last mammogram. Analyses will be carried out using generalized linear models. More specifically, logistic regression models will provide estimates of associations of factors (including the intervention groups) with the primary outcome of mammography screening and adjustment for possible confounders. For models over time with the panel data we will appropriately adjust for correlations using robust variance estimation.

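### The stated 90% power for the five-year trend does not follow from the plan's own 5,000 women per group at each year; the figure is too low, not too high

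*Protocol article*

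**What the plan says.** Three statements in the protocol article fix the size of the trend analysis.

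- **Women per year.** Under Power and Sample Size: "we estimated there would be at minimum 15,000 women available for the analyses involving the primary outcome at each year".
- **Allocation.** Under Overall design: "all eligible women are automatically enrolled and randomized 1:1:1 to the three study arms". This gives 5,000 per arm at each year.
- **Number of snapshots.** Also under Overall design: "This outcome will be determined at five times, at baseline and at the end of each intervention year".

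The power paragraph makes two claims. The first concerns the group comparison: "With 15,000 in the sample (5,000 per group) there is greater than 99% power to detect the differences proposed or larger ones across groups", said to hold in both scenarios (RL/RC/ETTC 75/80/85% and 80/83/86%). The second concerns time: "there will be approximately 90% power for an increasing trend over five years leading to a 5% increase in any group". The effect and the test for this second claim are "leading to a 5% increase in any group (e.g..75 to.80) based on Cochran-Armitage test of trend". The paragraph gives no separate sample size for the trend, and no alpha, sidedness or allowance for correlation.

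Under Primary Outcome Analysis, the plan is to estimate the trend within each arm and also to compare trends between arms. For that analysis it says: "For models over time with the panel data we will appropriately adjust for correlations using robust variance estimation".

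**The concern.** A rise from 75% to 80% is large when each of five time points has 5,000 women, so a power of only 90% looked out of line with the inputs printed just before it. The same paragraph credits 5,000 per group with more than 99% power for differences between groups as small as 3 points at one time point. A 5-point rise within a group, using five time points of the same size, should not do worse.

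What is at stake is how the trend analysis is read. Someone relying on the sentence would take 5 points as roughly the smallest rise that one arm could show reliably, when the planned numbers can show about half of that. The sentence also covers only the rise within one arm. The second hypothesis is about trends that differ between arms, and the paragraph gives no figure for that comparison.

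**Working it through.** **Inputs from the article.** 5,000 women per arm at each snapshot; five snapshots; 0.75 rising to 0.80; Cochran-Armitage test; stated power about 90%.

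**Assumptions.** Equal steps (0.75, 0.7625, 0.775, 0.7875, 0.80), scores x = −2, −1, 0, 1, 2, independent snapshots, and alpha 0.05 both two-sided (z = 1.960) and one-sided (z = 1.645).

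**Formula.** T = Σ x·p. Null variance V0 = p̄(1−p̄)·Σx²/n. Alternative variance V1 = Σ x²·p(1−p)/n. Power = Φ[(T − z·√V0)/√V1].

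**Step 1: the stated figure at the stated n.**

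- T = −2(0.75) − 0.7625 + 0.7875 + 2(0.80) = 0.125
- V0 = 0.775 × 0.225 × 10 / 5,000 = 0.00034875, so √V0 = 0.01867 and T/√V0 = 6.69
- V1 = 1.73844 / 5,000 = 0.00034769, so √V1 = 0.01865
- Two-sided power = Φ[(0.125 − 1.960 × 0.01867)/0.01865] = Φ(4.74), which is above 99.99%; one-sided power is higher still

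The 90% does not reproduce. Changing the shape does not rescue it: with the whole rise in a single step at the end, power is 99.96%, and with a single early step it is 99.97%. Nor does alpha 0.01 or a continuity correction.

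**Step 2: what n gives 90%?** The same formula, solved for n:

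| Women per snapshot | Two-sided 0.05 | One-sided 0.05 |
|---|---|---|
| 5,000 | >99.99% | >99.99% |
| 1,172 | 90.0% | 94.5% |
| 1,000 | 85.0% | 91.2% |
| 955 | 83.3% | 90.0% |

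The row of 1,000 is 5,000 divided by five snapshots. Entering 5,000 as the total over all snapshots, with a one-sided test, would give roughly the stated figure. That is a guess at the source; the article does not say.

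**Step 3: what rise has about 90% power at 5,000 per snapshot?** For 0.75 to 0.775, T = 0.0625, √V0 = 0.01903 and T/√V0 = 3.28. Two-sided power is 90.7%. The rise with about 90% power is therefore 2.5 points, half the 5 points stated.

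**Step 4: the between-arm trend.** Take one arm flat at 75% and the other rising in equal steps, with 5,000 per arm per snapshot, independence and two-sided 0.05. Here T = Σ x·(difference in p), and the variance is the sum of the two arms' V1.

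- 5-point difference by Year 4: T = 0.125, standard error 0.02688, ratio 4.65, power Φ(4.65 − 1.96) = 99.6%
- 3-point difference: T = 0.075, standard error 0.02710, ratio 2.77, power Φ(2.77 − 1.96) = 79%

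**Step 5: the group comparison.** At 5,000 per arm the three-group chi-square test (2 degrees of freedom) in scenario 2 has noncentrality 63.8 and power above 99.99%. Scenario 1 also exceeds 99% for the three-group test and for every pair. In scenario 2 the adjacent pairs, by two-sided z-test at 0.05, have 97.2% (80 v 83%) and 98.6% (83 v 86%); one-sided they have 98.7% and 99.4%.

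**The case against.** The best defence is that nothing depends on the figure. The stated power is lower than the true one, the number of women is set by the health plan's membership, and the article names the last-year comparison, not the trend, as its most important result. All of this stands, and it limits the point to a wrong number that should be corrected.

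A second defence is that 90% may contain an unstated allowance for the same women being counted at several snapshots. That would need a variance inflation of about 5,000/1,172 = 4.3 for the two-sided test, and nothing in the paragraph suggests one. Positive correlation within women would in fact raise the power of a within-arm trend on a complete panel, so it does not explain a lower figure. Using the Cochran-Armitage test as a planning approximation, with a robust-variance panel model for the analysis, is ordinary practice and no error in itself.

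Three stronger readings are tempting, and the document does not support them.

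- **That the figure of more than 99% is also wrong.** The sentence speaks of differences across groups, the wording also used for the main Year 4 comparison, and it reads naturally as the three-group test, for which the figure is correct. The adjacent pairs in scenario 2 fall short of 99% by less than 2 points, and only on an assumed two-sided pairwise reading.
- **That pairwise power should be cut further for multiple testing.** The article states no such rule.
- **That the sentence powers an analysis nobody planned.** The within-arm trend is itself a planned analysis. The gap is only that the between-arm comparison, also planned, has no figure.

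**Conclusion.** The point holds for the trend sentence alone. The article states about 90% power where its own inputs give more than 99.9%. Put as sample size, 90% fits 955 to 1,172 women per snapshot, not 5,000; put as effect size, the 5 points should be about 2.5. This rests on alpha 0.05, independent snapshots and equal steps, but the result at 5,000 per snapshot stays above 99.9% when the shape, sidedness or alpha (down to 0.01) is varied.

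The error is conservative. The trend analysis within an arm is amply powered, and no design or recruitment decision changes. The between-arm comparison of trends is well powered for 5 points and only moderately (79%) for 3 points, the lower end of the differences across groups that the article calls reasonable to expect. That figure depends on the independence assumption and on one arm staying flat.

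**What to change.** 1. **Correct the trend sentence.** State more than 99% power for a 5-point rise within a group at 5,000 women per snapshot, or about 90% for a 2.5-point rise. Give the number per snapshot, alpha and sidedness. If a smaller number or a variance inflation was intended, state it instead.
2. **Add power for the between-arm comparison of trends.** Under independence with one arm flat at 75%, this is about 99.6% for a 5-point and about 79% for a 3-point difference by Year 4. Name the assumptions beside the figures.
3. **Clarify the group comparison.** Label the figure of more than 99% as the three-group test. If pairwise power is wanted, add that the adjacent pairs in scenario 2 have about 97% and 99% at two-sided 0.05.

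The cost is a few rewritten sentences. No extra women, no change of design and no change of analysis are needed.

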#### Proportion needing repeat interventions

The comparison of rates of repeat interventions will be made between the two call arms of the study (RC and ETTC). We identified sufficient power (greater than 85%) for differences in proportion needing repeat intervention of 6% (80% vs. 86% for example).

### Statistical Methods

#### Primary Outcome Analysis: HEDIS-like measure over time

The unit of randomization and analysis is the individual woman. The primary outcome measure is the proportion of women continuously enrolled for 24 months with ≥1 mammogram in the past 24 months. This will be evaluated at the five measurement time points. The main study finding of interest will be the comparison of this proportion across groups after the last year of intervention (Year 4), because we believe this result best illustrates the magnitude of intervention effect that would be achieved in all future years. The second hypothesis is that the primary outcome measure may change differently over time in the telephone intervention groups because there may be some cumulative effect of repeated interventions on women who do not respond the first time. It is also possible that the interventions may become less effective when applied repeatedly to the same group of women over time. Changes in the composition of the patient population over time could also cause changes in the outcomes. We will estimate the trend over time of the primary outcome within each intervention group and compare the trends over time among the randomized groups. The third hypothesis is that lower age will be associated with a greater response to less intensive interventions. We will investigate this hypothesis through analyses assessing the interaction of subgroups and the intervention arms. To accomplish this and some related analyses involving the primary outcome, we will examine the interactions with intervention group of age, type of medical insurance, and time since last mammogram. Analyses will be carried out using generalized linear models. More specifically, logistic regression models will provide estimates of associations of factors (including the intervention groups) with the primary outcome of mammography screening and adjustment for possible confounders. For models over time with the panel data we will appropriately adjust for correlations using robust variance estimation.

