### Interventions

Only women ≥ 18 months from a mammogram receive study interventions. See Figure 2. When women are ≥ 18 months from their last mammogram, they all receive the same reminder letter. The letter is electronically signed by a woman's PCP and states: 1) there is no record of a mammogram in the last 18 months, 2) getting regular mammograms every 1-2 years is important and 3) her PCP recommends that she call the Study Scheduler for a mammogram appointment. When women call, the Study Scheduler uses the same script for all, except as noted below for women in the counseling arm. (See Table 2 for Study Scheduler Protocol)

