### Baseline results

Since July 2009, 18,509 female FCHP/FC enrollees aged 51-84 have been enrolled into our tracking database and were randomized into one of three arms. Table 6 shows their mammogram status at randomization. Table 7 shows the characteristics of the study sample, their approval or non-consent status by age. At baseline, 5,223 women were eligible for an intervention.

**Table 6 T6:** Mammogram Status at Study Entry*

Last Mammogram	<8 mo. ago	18-23 mo. ago	24-29 mo. ago	30-35 mo. ago	26-48 mo. ago	>48 mo. ago
N = 18,509 (100.0%)	12,808 (69.20)	986 (5.33)	866 (4.68)	599 (3.24)	851 (4.60)	1,758 (9.50)

* Columns do not total to 100% because of missing data

**Table 7 T7:** Characteristics of Study Sample

Age	Eligible women at baseline in study database*	Women opted out of intervention phase after broadcast letter	PCP approved for possible intervention phase	Women opted out of intervention phase at 1^st ^intervention attempt	Women eligible for reminder intervention study	Women >= 18 months from last mammogram and intervention eligible
50-59	5,901 (31.88)	30 (3.44)	5,826 (33.62)	12 (20.69)	5,814 (33.66)	1,842 (35.27)

60-69	4,781 (25.83)	115 (13.17)	4,613 (26.62)	13 (22.41)	4,600 (26.63)	1,146 (21.94)

70-79	5,429 (29.33)	494 (56.59)	4,818 (27.80)	15 (25.86)	4,803 (27.81)	1,329 (25.45)

80-84	2,398 (12.96)	234 (26.80)	2,074 (11.97)	18 (31.03)	2,056 (11.90)	906 (17.35)

Total	18,509	873	17,331	58	17,273	5,223

*All women 50-84 in FCHP for ≥24 months with current FC PCP and no mammogram in last 4 months

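### Hypothesis 3 concerns response to the interventions, but its age-by-arm test uses the all-women primary outcome, which also reflects how many women at each age can be contacted

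*Protocol article*

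**What the plan says.** The Statistical Methods section (Primary Outcome Analysis) sets out the hypothesis: "The third hypothesis is that lower age will be associated with a greater response to less intensive interventions". The method follows: "We will investigate this hypothesis through analyses assessing the interaction of subgroups and the intervention arms". The outcome for that analysis is the primary one, since the article goes on to say "we will examine the interactions with intervention group of age, type of medical insurance, and time since last mammogram" as part of the analyses of that outcome. The models are logistic regressions.

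Under Overall design, the denominator is everyone: "The primary outcome is the proportion of all women who have been enrolled for" at least 24 months. Under Interventions, exposure is much narrower: "Only women ≥ 18 months from a mammogram receive study interventions". Under Baseline results: "At baseline, 5,223 women were eligible for an intervention", out of 18,509 randomized.

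Two other planned analyses come close. An arm interaction with time since last mammogram is listed beside age, not jointly with it. The Secondary Outcomes Analyses include a mammogram within three months in women receiving an intervention for the first time, but age enters only as an adjustment covariate and hypothesis 3 is not mentioned. The Power and Sample Size section gives no power for any interaction.

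**The concern.** The hypothesis is about how women of different ages react to a letter or a brief call. The test asks whether the between-arm odds ratio in all women is constant over age. That odds ratio depends on response, on the share of women at each age who can be contacted, and on the screening rate in everyone else. If the contactable share varies with age, an interaction can appear without any age difference in response. A true age difference is also diluted by women who received nothing.

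Study goal 2 is to improve the efficiency and sequencing of the interventions by identifying patient factors, partly through subgroup analyses. An age interaction that reflects who was overdue, or a missed one that reflects dilution, would mislead that decision.

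**Working it through.** **Stated power.** The article's only between-arm figure is above 99% with 5,000 per arm. At two-sided 0.05, scenario 1 (75/80/85%) gives more than 99.9% for every pair. Scenario 2 (80/83/86%) gives more than 99.9% for the global test and for RL-ETTC, 97.2% for RL-RC and 98.6% for RC-ETTC. The figure essentially reproduces, but it says nothing about an interaction.

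**Inputs from Table 7.** N = all women, E = eligible for the reminder study, O = overdue and intervention-eligible.

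| Age | N | E | O | O/N |
|---|---|---|---|---|
| 50-59 | 5,901 | 5,814 | 1,842 | 31.2% |
| 60-69 | 4,781 | 4,600 | 1,146 | 24.0% |
| 70-79 | 5,429 | 4,803 | 1,329 | 24.5% |
| 80-84 | 2,398 | 2,056 | 906 | 37.8% |
| Total | 18,509 | 17,273 | 5,223 | 28.2% |

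The O column already nets out exclusions and opt-outs.

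**Mixing, without a model.** An all-women RC-RL difference of 5 points means 5/0.282 = 17.7 points among overdue women. If that 17.7 holds at every age, the all-women differences are 17.7 × O/N = 5.5, 4.2, 4.3 and 6.7 points. That is a spread of up to about 2.4 points with no age difference in response.

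**Model for the rest (assumed values).** The all-women rate in an age band and arm is [(N−E)u + (E−O)v + O·r]/N. Here u = 30% screened if not in the reminder study, v = 95% if on schedule, r is response in overdue women, each arm has one third of the women, and alpha is 0.05. The test is the likelihood-ratio test of age-by-arm in a logistic model, with 6 df for four bands and 2 df for linear age. Power is from the noncentral chi-square.

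**Equal response at every age.** Take r = 17/33/50% (RL/RC/ETTC).
- Age 50-59, ETTC: (87×0.30 + 3,972×0.95 + 1,842×0.50)/5,901 = 80.0%. RL: the same with 0.17 = 69.7%. Difference 10.3 points.
- The four differences are 10.3, 7.9, 8.1 and 12.5 points. The all-women odds ratios are 1.74, 1.59, 1.50 and 1.71, while in overdue women the odds ratio is 4.88 in every band.
- The all-women test rejects about 16% of the time with four bands (12-19% for u from 60% down to 10%) and about 10% with linear age.
- For effects of 3-6 points, rejection is about 5-10%, depending on age coding.

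**Response that differs by age.** RL falls from 35% (50-59) to 20% (80-84), RC from 40.5% to 33%, ETTC stays at 50%. Lapse means the share of on-schedule eligible women who later become exposed. Linear-age power:

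| Lapse | All women | Exposed women |
|---|---|---|
| 0% (baseline share) | about 22% | 94% |
| 30% | about 50% | 99% |
| 50% | about 72% | over 99% |

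With a 25-point RL gradient, all-women power is about 63% at the baseline share and 96% with 30% lapse.

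**Second check, two age groups, risk-difference scale.** RC-RL gains of 12.7 and 22.7 points, r = 25-35%, and 90-95% screened in the others. Power in overdue women against all women is 77-81% against 38-45% (split at 70) and 74-78% against 20-23% (split at 60). With twice the overdue share it is 97-98% against 84-87%, and 96-97% against 52-55%.

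**The case against.** Table 7 is a snapshot at study entry, whereas the main result is at Year 4, after weekly eligibility searches and repeat contacts. The article itself reports repeat mammography below 50% and regular screening in only 46% of women, so many on-schedule women will later become exposed. This stands, and it is why the power loss must be shown over a range of lapse.

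The inflation is small for effects near scenario 2 and depends on age coding, which a condensed article may leave to the analysis plan. With linear age or a cut at 70 there can be little mixing, because the overdue share is U-shaped in age (28.0% under 70, 28.6% at 70 and over). This also stands.

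Opt-out and exclusion rise with age (1.5%, 3.8%, 11.5% and 14.3% not in the reminder study). They are not a further channel to add to the overdue-eligible share, because that share has already removed these women.

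The all-women interaction is a legitimate quantity for a health plan, the primary comparison is unaffected, and goal 2 also draws on intermediate outcomes. All true. None of it supplies an age-by-arm test among women who could respond, and the neighbouring analyses do not either.

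**Conclusion.** The mismatch is in the text: a hypothesis about response is tested in a population most of whom, at baseline, could not respond, and the share who could varies from 24.0% to 37.8% by age. The planned interaction mixes response with exposure.

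A reader might infer that the test loses most of its power, or that a true age difference will usually be missed. The documents do not support that as a general statement. They give no age gradient, no lapse rate and no alpha for this test. All-women power runs from about 22% to 72% for one gradient as lapse goes from 0 to 50%, and reaches 96% for a larger gradient with 30% lapse. A reader might also infer that some 70% of women receive nothing throughout the trial, but that share applies to study entry only.

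What holds is a modest false-positive inflation that grows with the arm effect, and a power loss that can be substantial. Both sizes rest on the assumed screening rates, response rates and alpha of 0.05. This is a worthwhile, inexpensive correction to a secondary question and does not threaten the main comparison.

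**What to change.** Test hypothesis 3 with an age-by-arm logistic interaction, by randomized arm, in approved women who had not opted out after the broadcast letter. Start each woman at the first date she is at least 18 months from her last mammogram. That date precedes any arm-specific contact, so randomization is preserved.

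- Use one outcome window from that date in all three arms, long enough to cover the whole ETTC sequence (letter, second letter with booklet, call attempts). The existing three-month outcome would need rewording: the Outcomes section ties it to the interventions generally, the Secondary Outcomes Analyses to telephone interventions.
- Keep women who opt out at first contact (58 in Table 7).
- Do not restrict to women overdue at Year 4, because that selects on a post-randomization result.
- Keep the all-women Year-4 age interaction and label it a description of population impact by age.

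The cost is a few lines of analysis text and one extra model on data already held: mammogram dates, birth dates, approvals and opt-outs. The drawback is that the result applies to overdue women rather than to the whole membership, which the retained all-women analysis covers.
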